### Design

This study will be a 6-month single-blinded randomized controlled trial (RCT) with a 6-month follow up, that will be performed in special schools for children with disabilities and pediatric physiotherapy practices in the Netherlands, between September 2009 and February 2012. Within each school or practice, participants will be randomly assigned to either the intervention group or the control group. A blinded independent researcher will provide the allocation sequence in sealed envelopes. For schools and practices with five or more participants, children will be stratified for GMFCS level (I *vs*. II/III) before randomization. Group allocation will only be revealed to the parents after the baseline measurements. The assessors are blinded for group allocation during the entire study period. The children and parents will be instructed not to tell the assessors which group they are assigned to. The study protocol has been approved by the Medical Ethics Committee of the VU University Medical Center in Amsterdam.

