### Statistical analysis

A sample-size calculation revealed that at least 22 children in each group are required to detect a difference in improvement of 1,000 steps per day between the intervention and the control group on the primary outcome. The power was 0.8, and the alpha was set at 0.05. This increase in steps per day seems to be clinically relevant, since improved health outcomes have been reported in adults after an increase of 1,000 in the amount of steps per day[54]. Taking into account drop-outs, 25 children will be included in each group.

Student *t*-tests will be performed to evaluate group differences at baseline, and a random coefficient analysis[55] will be performed to determine differences in change over time (treatment effect) between the control group and the intervention group. This method takes the dependency of children within physiotherapy practices and schools into account. An intention-to-treat analysis will be performed. The primary outcome (physical activity) and secondary outcomes (fitness, capacity of mobility, social participation, and health-related quality of life) will be the dependent variables in the analysis, with group allocation (control group or intervention group) and measurement occasion (time) as independent variables. The intervention effect will be evaluated by the group * time interaction. The alpha is set at 0.05. The influence of age, gender, and disease and environmental characteristics on the treatment effect will be investigated, and, if necessary, included as covariates in the analysis. The data will be analyzed with the Statistical Package for the Social Science, version 15.0 (SPSS Inc, Chicago, Illinois, USA).

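### Taking the group-by-time interaction as the effect, with no adjustment for the T0 value, makes this a change-score analysis: valid, but less precise than a baseline-adjusted one by (1−ρ)/2 under equal variances

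*Protocol article*

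**What the plan says.** All of this is in the Protocol article.

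- **Model terms** (Statistical analysis): a random coefficient analysis "with group allocation (control group or intervention group) and measurement occasion (time) as independent variables".
- **Effect** (same section): "The intervention effect will be evaluated by the group * time interaction". The purpose is given as "to determine differences in change over time (treatment effect) between the control group and the intervention group".
- **Covariates** (same section): age, sex and the disease and environmental descriptors may be added if this proves necessary. The Procedure section lists those descriptors, and the T0 value of the outcome is not among them.
- **Use of baseline** (same section): the arms are compared at T0 by t-tests, which adjust nothing.
- **Timing of T0** (Design): "Group allocation will only be revealed to the parents after the baseline measurements".
- **Sample size** (Statistical analysis): the calculation aims "to detect a difference in improvement of 1,000 steps per day between the intervention and the control group on the primary outcome". Its result is 22 per arm, for 80% power at a significance level of 0.05, raised to 25 per arm as an allowance for attrition.

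**The concern.** T0 is measured before families learn their allocation, and allocation is random, so the two arms have the same expected T0 mean. A model with a group main effect, time and their interaction still estimates a separate T0 mean for each arm and subtracts the observed T0 difference in full. Because T0 predicts follow-up imperfectly, only part of a chance T0 difference carries over to follow-up. Subtracting all of it adds noise.

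The article fixes the model terms and the effect parameter, so this is a stated choice and not a detail left for another document. At stake is the width of the confidence interval in a trial of 50 children. The same model serves all primary and secondary outcomes.

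**Working it through.** **Inputs.** From the article: a target of 1,000 steps/day on the improvement scale, 22 per group, power 0.80, alpha 0.05. Assumed: a two-sided test, equal SD s at T0 and follow-up, one follow-up time, and ρ. The article gives no SD and no ρ.

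**1. The plan's own figure.** Without an SD, the 22 per group cannot be reproduced independently; it can only be solved backwards.

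SD of change = 1,000 / (1.960 + 0.842) × √(22/2) ≈ 1,184 steps/day (two-sided, normal approximation).

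A two-sided t calculation gives about 1,157, and a one-sided normal one about 1,334. Going from 22 to 25 matches about 12% drop-out (22/0.88 = 25).

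**2. What the interaction estimates.** The model with group, categorical time and their interaction was fitted to one complete simulated data set (T0, T6, T12; 22 per group). The T6 interaction coefficient was 1066.592, and the difference in mean change from T0 to T6 was also 1066.592.

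**3. Precision.** Per-child variances are:

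- change score: 2s²(1−ρ)
- baseline-adjusted: s²(1−ρ²)
- ratio, adjusted to change: (1+ρ)/2, so the information lost is (1−ρ)/2

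The table holds the SD of change at 1,184. The adjusted SD is 1,184 × √((1+ρ)/2).

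| Assumed ρ | Loss | Adjusted SD | n per group for power 0.80 | Power at 22 per group |
|---|---|---|---|---|
| 0.3 | 35% | 954 | 15 | 0.94 |
| 0.5 | 25% | 1,025 | 17 | 0.90 |
| 0.6 | 20% | 1,059 | 18 | 0.88 |
| 0.7 | 15% | 1,091 | 19 | 0.86 |
| 0.8 | 10% | 1,123 | 20 | 0.84 |
| 0.9 | 5% | 1,154 | 21 | 0.82 |

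Starting from 1,157 with a t test on 41 degrees of freedom, power for ρ of 0.5 to 0.8 is 0.898, 0.879, 0.859 and 0.839, in agreement.

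**4. Cost of estimating the baseline slope.** With 44 children the adjusted variance grows by a factor of about 1 + 1/40 = 1.025. The loss becomes 1 − 0.75 × 1.025 = 23% at ρ = 0.5 and 1 − 0.90 × 1.025 = 8% at ρ = 0.8. In 20,000 simulated trials per value, the net loss was 24% (ρ = 0.5), 16% (0.65) and 8% (0.8), and both estimators were unbiased. Power with this cost is Φ(2.802/√0.769 − 1.960) ≈ 0.89 at ρ = 0.5 and Φ(2.802/√0.9225 − 1.960) ≈ 0.83 at ρ = 0.8.

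**5. Sensitivity to the other assumptions.** If the follow-up SD is k times the T0 SD, the loss is 1 − k²(1−ρ²)/(1 + k² − 2kρ). For ρ from 0.8 to 0.5:

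- k = 1.2: 0.3 to 13%
- k = 0.8: 36 to 43%
- k = 1, effect averaged over T6 and T12 with all correlations equal to ρ: 13 to 33%

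**6. Illustration only.** Take ρ = 0.6, an SD of change of 1,157 and a chance T0 difference of 0.3 SD. Then s = 1,157/√0.8 ≈ 1,293, and the change-score estimate is shifted by (1 − 0.6) × 0.3 × 1,293 ≈ 155 steps/day. This is the loss in step 3 seen conditionally on one imbalance, not a further harm.

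**The case against.** The strongest defence is that nothing here is wrong. The trial is powered on a difference in improvement and analysed as a difference in change, so target, sample size and analysis agree. Under randomisation the estimate is unbiased and the test keeps its type I error. That stands, and it limits the point to precision forgone.

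A second defence is that part of the reading is inferred. The article does not say outright that T0 is in the outcome vector. However, a model whose interaction measures change over time needs T0 as its first occasion. If time were fitted as linear, the interaction would be a difference in slopes and the formulas above would not apply exactly, but it would still lack baseline adjustment. A condensed article may leave parametrisation to a fuller document, but this one names the terms and the effect, and those would have to change.

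A third defence is that the size is uncertain. This stands too: no SD or correlation is given, and the loss can be close to nil if follow-up is more variable than T0.

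A reader might go further and infer that randomising within small sites makes baseline imbalance likely. The article does not support this. Sites with five or more participants stratify by GMFCS level, and the Outcome measures section says the step monitor separates those levels, so where it applies stratification should help balance baseline steps.

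**Conclusion.** The concern holds as a matter of efficiency. The stated model gives a difference in mean change from T0 and leaves the equality of expected T0 means unused. With equal variances and one follow-up time this costs (1−ρ)/2 of the information. At 22 per group, power would be about 0.90 to 0.84 for ρ of 0.5 to 0.8 instead of 0.80, or roughly 0.89 to 0.83 after the slope cost.

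Three stronger readings do not follow. The trial is not shown to be biased or underpowered against its own target. A loss of 10 to 25% is not a fact about this trial: it needs ρ of 0.8 to 0.5, equal variances and a single follow-up. The 155 steps/day is an illustration built on a back-solved SD, an assumed ρ and a chosen imbalance, and should not be cited as an expected bias. The change is worth making because it costs almost nothing, not because the planned analysis is invalid.

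**What to change.** State in the Statistical analysis section that, for all primary and secondary outcomes, the effect is estimated with adjustment for baseline, in one of two ways:

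- take the post-baseline occasions available for that outcome as the dependent variable, with its T0 value as a covariate; or
- keep T0 as an outcome and constrain the arms to a common T0 mean, by omitting the group main effect and keeping time and group by post-baseline occasion.

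The random effects for child and for practice or school can stay as planned. The adjustment should be fixed in advance and should not depend on the baseline t-tests.

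The cost is one sentence. T0 is already measured, no further children or visits are needed, and both forms can be fitted in the named software. The sample size can stay as it is; the gain appears as extra precision.

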### Outcome measures

The primary outcome of this study is physical activity. Physical activity will be measured objectively with the StepWatch™Activity Monitor 3.0 (StepWatch) (Cyma Corporation Seattle WA, USA) as well as subjectively with self-reports: the Activity Questionnaire for Adults and Adolescents (AQuAA), and the Children's Assessment of Participation and Enjoyment (CAPE).

*The StepWatch *is an ankle-worn bi-axial accelerometer (frontal-sagittal plane) that registers the number of steps per minute. The StepWatch can accurately record steps for different gait styles, because the sensitivity settings are calibrated for each child individually. Before each registration period, the sensitivity settings will be calibrated by comparing manual counts of a 50-step walk with StepWatch recordings. The settings will be adjusted until an agreement of > 95% is reached between manual counting and the StepWatch registration. Children will wear the StepWatch for seven consecutive days during all waking hours, except when swimming and bathing. During the registration period, the parents will fill in a weekly diary to register the child's daily activities and the weather conditions. The StepWatch is valid for children with CP, and able to discriminate between activity levels of children with different GMFCS levels[7].

*The AQuAA *is a reliable questionnaire to assess physical activity as well as sedentary behavior[35] in adolescents and adults. It is derived from the valid and reliable Dutch Short Questionnaire to Assess Health-Enhancing Physical Activity[36], but questions about sedentary behaviours were added and the recall period was specified as "the past seven days"[35]. The parents will have to rate how many days, and how much time per day the child spent on transportation to and from school, activities at school and at home, as well as leisure time activities and sports in the past seven days. The parents will also have to indicate how strenuous (light/moderate/vigorous) these activities were. For the purpose of the present study the examples of activities will be adapted, so that they are relevant for school-aged children.

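### Covariates may enter the primary model after their influence on the treatment effect has been seen, and GMFCS level, a randomisation stratum at larger sites, is only one of the conditional candidates

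*Protocol article*

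**What the plan says.** All of this is in the protocol article.

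- **Model (Statistical analysis).** The random coefficient analysis is specified "with group allocation (control group or intervention group) and measurement occasion (time) as independent variables", and "The intervention effect will be evaluated by the group * time interaction". On site, the article says: "This method takes the dependency of children within physiotherapy practices and schools into account".
- **Covariates (same section).** "The influence of age, gender, and disease and environmental characteristics on the treatment effect will be investigated, and, if necessary, included as covariates". No threshold or procedure defines when inclusion becomes necessary.
- **Baseline (same section).** Student t-"tests will be performed to evaluate group differences at baseline". The text does not connect these tests with the choice of covariates.
- **Candidates (Procedure).** The disease characteristics are GMFCS level, FMS, MACS, unilateral or bilateral involvement, and selective motor control. The environmental characteristics are school type, living environment, family structure, socio-economic status, parental stress and support, and parental physical activity.
- **Randomisation (Design).** Allocation is made within each school or practice. At those with five or more participants, "children will be stratified for GMFCS level" (I versus II/III).
- **StepWatch (Outcome measures).** The device is described as "able to discriminate between activity levels of children with different GMFCS levels".

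**The concern.** Two different things are joined in one sentence. Whether a characteristic influences the treatment effect is a question of effect modification and is answered with a covariate-by-group-by-time term. Including it as a covariate is adjustment, which serves precision and should not depend on what the effect turns out to be. An analyst could follow either reading.

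On the adjustment reading, the analyst inspects how the estimated effect moves as each candidate is tried and then settles the model. The reported p-value no longer belongs to one model fixed in advance, and two analysts could reach different primary results from the same data.

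GMFCS level was important enough to stratify on, and the article itself links it to the level of StepWatch activity. Even so, it enters only through this conditional route.

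**Working it through.** **1. Number of candidates.** Age and gender (2) + disease items (5) + environmental items (6, or 7 if parental stress and support are counted separately) = 13 or 14.

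**2. Sample size.** The article's figure is 22 per group for a difference of 1,000 steps per day, with power 0.8 and alpha 0.05. No standard deviation is given, so 22 can only be solved backwards. Assuming a two-sided test, SD = 1000 / [(1.960 + 0.842) × √(2/22)] ≈ 1,184 steps per day. This is an assumption used below, not a figure from the article. Recruiting 25 per group matches 22/(1 − 0.12) = 25. The evaluable number is therefore about 2 × 22 = 44.

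**3. Screening for modifiers.** Assuming independent tests at 0.05, the chance of at least one spurious modifier is 1 − 0.95^13 = 0.49 or 1 − 0.95^14 = 0.51. This is the error rate of the screen, not of the primary test. The screen would also miss most real modifiers. For a two-level characteristic split evenly, the interaction contrast has twice the standard error of the main contrast. An interaction as large as the main effect therefore has standardised size (1.960 + 0.842)/2 = 1.40, and power of about Φ(1.40 − 1.96) ≈ 0.29.

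**4. What selection does to the primary test.** This depends on how covariates enter.

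- *Main effects only.* The group-by-time estimate rests on within-child change, and a time-constant covariate shifts every occasion of a child equally, so it cancels. In a random-intercept check (44 children, 3 occasions, 14 covariates with total R² of 0.2 on level, 60 datasets, all assumed), adding any single covariate to complete data moved the estimate by at most 5e-15. With 12% of post-baseline visits missing, the largest p-value shift within a dataset had median 0.015 and maximum 0.05. The proportion of results below 0.05 did not change.
- *Covariate-by-time terms, or a change score.* The table gives simulated type I error with 22 per group and no true effect. Covariates are independent and normal; their number and R² are assumptions.

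| Rule | 5 or 10 candidates (R² 0 or 0.3) | 13–14 candidates (R² 0.2) |
|---|---|---|
| Full set fixed in advance | 0.049–0.053 | not run |
| Selected by baseline t-test | 0.039–0.055 | not run |
| Kept if the estimate moves by more than 10% | 0.046–0.074 | 0.064–0.070 |
| Smallest p among the unadjusted and single-covariate models | 0.076–0.106 | 0.103–0.112 |

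**5. GMFCS.** If GMFCS explains a share R² of the variance in *change*, residual SD becomes 1,184 × √(1 − R²). Power at 22 per group goes from 0.80 to 0.82, 0.84 and 0.88 for R² of 0.05, 0.10 and 0.20. Leaving out a balanced prognostic stratum made the unadjusted test conservative: type I error was 0.042 at R² 0.10 and 0.029 at 0.20, against 0.052 and 0.051 when adjusted. The article says nothing about R² for change.

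**6. Baseline t-tests.** Under proper randomisation any baseline difference is due to chance. With 10 independent tests, the chance of at least one significant result is 1 − 0.95^10 = 0.40.

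**The case against.** The strongest objection is that the error rates in the table do not belong to the model as literally written. Time-constant covariates added as main effects barely touch a group-by-time test. **This stands**, and it limits both the size of the problem and the form of the fix.

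Other points on that side:

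- *A reader might infer that the plan leaves GMFCS out of the model, or does not analyse the trial as randomised.* The article does not support this. GMFCS heads the list of disease characteristics and so is a candidate. Stratification on it applies only at sites with five or more participants. School or practice, the factor that applies to every child, is handled by the random coefficient analysis.
- *A reader might infer that the baseline t-tests choose the covariates, or are applied to categorical items.* The text says neither. The tests are uninformative but do not bias the effect.
- *A reader might infer that omitting GMFCS inflates type I error.* It does the reverse if GMFCS is prognostic for change: the test becomes conservative.
- *A condensed article may leave the selection criterion to an analysis plan.* That would excuse a missing threshold. It does not excuse the rule that is printed, which names influence on the treatment effect as the ground for inclusion.
- *The sentence could mean exploratory effect modification only.* The first half allows this, but the second half then places the same variables in the analysis as covariates.

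**Conclusion.** The point holds in limited form. The printed rule lets the primary model depend on the observed treatment effect, with 13 or 14 candidates for about 44 evaluable children. It also merges effect modification with adjustment and leaves a randomisation stratum as a conditional term.

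The effect on type I error cannot be given as one number. It is nil when covariates enter as main effects and data are complete. With covariate-by-time terms or a change score, it ranges from no inflation to roughly 6–7% under a 10% change-in-estimate rule, and up to about 11% if the most favourable model is kept. The top figure is a worst case; the article does not state that rule. These results rest on assumed numbers of covariates, R² values and selection rules.

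A power gain from GMFCS should not be claimed as fact. The article relates GMFCS to the level of activity, not to change. The 0.82–0.88 range is conditional on GMFCS explaining 5–20% of variance in change and on the back-solved SD. The case for the fix rests on a model settled in advance and on carrying the stratum into the analysis.

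**What to change.** Replace the conditional covariate sentence with a fixed primary model:

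- Include GMFCS level (I versus II/III) for all children, entered with its time interaction. Alternatively, model the follow-up values adjusted for baseline, with GMFCS as a covariate. A GMFCS main effect alone would leave the group-by-time test unchanged when data are complete.
- Keep school or practice as already planned.
- Label any study of effect modification exploratory. Name the characteristic, use a covariate-by-group-by-time term, and state that its result does not alter the primary model.
- Drop the baseline significance tests and present baseline characteristics descriptively by group.

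The cost is a few sentences and no new data, since GMFCS level is already recorded. The model loses one degree of freedom in the baseline-adjusted form and two with GMFCS plus its interaction with a linear time term. If time is categorical, each further follow-up occasion costs one more.

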## Discussion

This is the first study of children with CP that investigates the effects of a combined intervention on physical activity, by focusing on a change in lifestyle and improvement in fitness. The separate elements of the intervention (lifestyle intervention [counseling and home-based physiotherapy] and fitness training) are expected to reinforce improvements in fitness and physical activity, resulting in sustained effects on physical activity one year after the start of the intervention. Temporary effects of the fitness training are expected to be maintained by changes to an active lifestyle in daily life and in the home situation. In turn, children may be able to maintain an active lifestyle if they have better levels of fitness and continue to perform more physical activities in their own environment.

A possible limitation of the study is that effects cannot be assigned to a specific element of the intervention. However, by assessing both physical activity and fitness outcomes, as well as the attitude of the child and the parents towards physical activity, more insight can be gained in the inter-relationship of these outcomes.
